## 7.2 Randomisation, blinding and treatment allocation

Patients, who are eligible for the trial and who give informed consent for participation in the trial, will be randomized to a ‘nurse-led self-help plus usual care’ or ‘usual care alone’ therapy. Randomisation will take place at the level of the patient. Stratification variables will be the number of previous depressive episodes (cut off point at 4 or more episodes in the last 5 years) and the type of treatment received for the last recurrent episodes. It is not possible to blind patients or healthcare providers to the intervention in this study due to the nature of the intervention.

## 7.3 Study procedures

The research assistant checks in- and exclusion criteria. ‘Being remitted’ in this trial is defined as a score of < 10 on the 17-item Hamilton Depression Rating Scale. In order to assess the severity of residual symptoms a baseline, Q-IDS-SR score is calculated. In general, a score of 0-5 represents ‘normal/ no depression’ and a score 6-10 represents ‘mild depression’. A score of 11-15 indicates ‘moderate depression’, 16-20 ‘severe depression’ and 21-27 ‘very severe depression’.

After signing informed consent demographic data and the medical history are collected as part of routine care and in order to enable stratification. After randomisation, the nurse invites intervention subjects into the practice for an initial motivational face-to-face meeting about the course of depression and strategies to prevent recurrence. Also the nurse-led self-help therapy is explained.

Primary outcome is the (repeat) incidence of depressive disorder according to an independent and blinded Structured Clinical Interview for DSM-IV (SCID) 40 at 3, 6 ,9, 12 and 15 months. Secondary outcome is the Four Dimension Symptom Questionnaire (4-DSQ) 31, used every 3 months to assess co-morbid levels of self-reported distress, anxiety symptoms and levels of physical symptoms (somatisation). Satisfaction is measured with the Client/Patient Satisfaction Questionnaire (CSQ-8)46. The CSQ-8 is only assessed at 15 months in 20 ‘experimental’ patients who responded best, and 20 ‘experimental’ patients who responded worse (in terms of recurrences). Satisfaction is best linked to effectiveness this way.

Generic health-related quality of life is measured using both the EuroQol43 and SF-1244. QALYs will be calculated based on the EuroQol using the Dutch tariff by Lamers et al47 . Cost data related to health care uptake will be measured using the TIC-P 45. Medical costs that will be assessed include costs related to the intervention, medication use, hospital admissions, and contacts with healthcare professionals. Unit resource use will be multiplied by their appropriate integral cost prices47. Cost data stemming from absenteeism and presenteeism from paid work will be collected with the PRODISQ. Costs of productivity losses will be estimated using the friction cost method. In a secondary analysis, the human capital will also be used to estimate productivity losses. All questionnaires are assessed at 3, 6, 9, 12 and 15 months.

SES is measured by asking for level of education. Also items on self-efficacy in preventing depression which predict future risk for depressive disorder are obtained. These items are assessed at baseline, 6 and 12 months.

For an overview of assessments at baseline, during the intervention and during follow-up, see table 1. Collecting of data through questionnaires and analyzing the data is done by the main researcher and the research assistant who are not blinded.

Casefinding in this trial should not be a problem as these high risk patients are often seen by the PCP and are rather easily diagnosed with recurrent depression in the long term. Hence, inclusion should not be endangered.

**7.3.1 Informed consent**

Eligible patients that are found through a search in the database receive a global study information letter with 4 questions, including if the patient agrees upon receiving detailed information about the study. If the patient is interested in participating then the participant will contact the researcher or the researcher will contact the patient after 2 weeks and checks interest in participation. Subsequently, the researcher checks that the participant signs an informed consent for screening.

When global screening is positive, patients are sent a complete study information letter and an informed consent for participation in the trial. Definite inclusion / and exclusion criteria are checked through telephone-interviews and when the informed consent for participation in the trial is received the patient will enter the trial.

Consenting patients are asked to provide information about their socio-economic and demographic background and are assessed for their eligibility in more detail using semi-structured clinical interviews (SCID-I, HRSD-17 by phone) and self-report questionnaires.

## 7.4 Withdrawal of individual subjects

Participants can withdraw from treatment or from the study at any time. Nevertheless we ask those who withdraw from any arm if they are willing to attend all the remaining research appointments or at least to provide minimal data.

### 7.4.1 Specific criteria for withdrawal

Subjects who relapse into depression during the course of the intervention will be encouraged to continue the therapy. Besides, possible adjustments in the actual treatment will be started after consultation of the PCP. Patients who don’t want to continue, will be referred by the nurse to specific parts of the self-help in order to promote ongoing prevention of relapse. Subjects in the non-experimental group who relapse will continue their care as usual.

## 7.5 Replacement of individual subjects after withdrawal

Patients who discontinue the intervention are not replaced (and analysis is conducted in agreement with the intention to treat principle). Patients who skipped a measurement at one time point are approached for the next (thus causing only wave non-response), unless they withdraw.

##

## 7.6 Follow-up of subjects withdrawn from treatment

We will encourage those who withdraw from any arm if they are willing to attend all the remaining research appointments or at least to provide minimal data and are encouraged to continue participation. Besides, early drop-outs will be contacted by phone in order to ask for their motivation to quit (exit-conversation). Data of withdrawn patients will remain included in the statistical analysis.

## 7.7 Premature termination of the study

Premature termination of the study is possible in case of advice to do so from the monitoring committee. If the study is prematurely terminated the Medisch Etische Toetsings Commissie (METC), Bevoegde Instantie (BI) and College ter Beoordeling Geneesmiddelen (CBG) will be notified.

**Table 1 Overview of questionnaires**

| Measure | Description | T0 | T1 | T2 | T3 | T4 | T5 |
| --- | --- | --- | --- | --- | --- | --- | --- |
| ***Interviews*** |  | | | | | | |
| SCID-I | DSM-IV-TR Axis I  Disorders | + | + | + | + | + | + |
| HRSD-17 | Depressive symptoms  and severity | + | + | + | + | + | + |
| ***Self report measures*** |  | | | | | | |
| Q-IDS-SR | Depressive symptoms | + | + | + | + | + | + |
| EQ-5D | Quality of life | + | + | + | + | + | + |
| SF-12 | Quality of life | + | + | + | + | + | + |
| TIC-P | Direct / indirect costs | + | + | + | + | + | + |
| 4DSQ | Comorbid psychopathology | + | + | + | + | + | + |
| FSS | Severity of fatigue | + | + | + | + | + | + |
| MPQ-DLV | Severity / evaluation of pain | + | + | + | + | + | + |
| General self-efficacy scale | Self-efficacy | + | + | + | + | + | + |
| MAQ | Medication Adherence | + | + | + | + | + | + |
| Nemesis Somatic illnesses list | List of somatic disorders | + |  | + |  |  | + |
| CSQ-8 | Satisfaction |  |  |  |  |  | + |
| Life-chart | Course of symptoms | + |  |  |  |  |  |

T0=baseline, T1=3 month, T2=6 months, T3 = 9 months, T4= 12 months, T5 = 15 months

# 8. SAFETY REPORTING

## 8.1 Section 10 WMO event

In accordance to section 10, subsection 1, of the WMO, the investigator will inform the subjects and the reviewing accredited METC if anything occurs, on the basis of which it appears that the disadvantages of participation may be significantly greater than was foreseen in the research proposal. The study will be suspended pending further review by the accredited METC, except insofar as suspension would jeopardise the subjects’ health. The investigator will take care that all subjects are kept informed.

## 8.2 Adverse and serious adverse events

Adverse events are defined as any undesirable experience occurring to a subject during the study, whether or not considered related to the experimental treatment. All adverse events reported spontaneously by the subject or observed by the investiga­tor or his staff will be recorded.

A serious adverse event is any untoward medical occurrence or effect that at any dose:

- results in death;
- is life threatening (at the time of the event);
- requires hospitalisation or prolongation of existing inpatients’ hospitalisation;
- results in persistent or significant disability or incapacity;
- is a congenital anomaly or birth defect;
- is a new event of the trial likely to affect the safety of the subjects, such as an unexpected outcome of an adverse reaction, lack of efficacy of an IMP used for the treatment of a life threatening disease, major safety finding from a newly completed animal study, etc.

In this trial, serious adverse events related to the investigational treatment are relapse into depression with or without suicidal thoughts or the start of any other psychopathology (i.e. anxiety disorder). Hospitalisation might be necessary depending on the severity of the symptoms. No specific somatic disorders are expected during the course of this intervention.

All SAEs will be reported through the web portal *ToetsingOnline* to the accredited METC that approved the protocol, within 15 days after the sponsor has first knowledge of the serious adverse reactions. SAEs that result in death or are life threatening should be reported expedited.

The expedited reporting will occur not later than 7 days after the responsible investigator has first knowledge of the adverse reaction. This is for a preliminary report with another 8 days for completion of the report.

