## Prior to the start of the therapy, a face-to-face meeting with the nurse is planned at the primary care practice (at a maximum of 30 minutes). This meeting involves motivational interviewing, psycho-education on (the course and treatment of) recurrent depression, and an introduction to the nurse-led self-help therapy on the basis of the treatment manual. Apart from this face-to-face meeting there is weekly telephone contact (at a maximum of 15 minutes), initiated by the nurse. During these telephone meetings patients are asked several questions based on a rather strict protocol. These questions comprise: 1) did you fill out Q-IDS-SR questionnaire? 2) did you read and understand the literature belonging to that week? 3) did you make the accompanying **assignments?** and 4) what difficulties did you experience in your assignments? After these 3 questions, patients are shortly prepared for next week’s literature and **exercises**. The contact is of a supportive and facilitating nature and not of a psychotherapeutic nature.

If a nurse notices depressive symptoms during a regular phone-contact or a patient brings up feeling depressed, the nurse emphasizes specific parts of the therapy in order for the patient to cope with these symptoms. Only in the case of a patient expressing suicidal symptoms, the PCP should be notified. These procedures are made explicit in the informed consent papers.

After each contact the nurse summarizes the conversation in a journal on the basis of a checklist. The checklist includes 6 questions:

1) Did the patient fill out the Q-IDS-SR questionnaire of that week?

2) Did the patient read and understand the literature belonging to that week: (yes/no)

- lack of time

- feeling too depressed

- too difficult/did not understand - didn’t feel like

- other …

3) Did the patient make the accompanying assignments: (yes/no)

- lack of time

- feeling too depressed

- too difficult/ did not understand - didn’t feel like

- other …

4) What difficulties did the patient experience? (open)

5) How long did the conversation take (in minutes)

6) What consecutive number is this telephone contact (1 / 2 / 3 / 4 / 5 / 6 / 7 / 8)

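### Section 8.2 collects adverse events passively although one arm has nine extra nurse contacts, and no step is stated for reviewing TIC-P hospital admissions as possible SAEs in either arm

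*Protocol*

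**What the plan says.** Protocol 8.2 defines an adverse event as "any undesirable experience occurring to a subject during the study, whether or not considered related to the experimental treatment", so events of any cause in either arm are in scope. Capture is passive: such events "reported spontaneously by the subject or observed by the investiga­tor or his staff will be recorded". Neither Table 1 nor the text of 7.3 lists an adverse event question or form.

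Contact differs by arm. Under 5.1, before the therapy starts "a face-to-face meeting with the nurse is planned at the primary care practice", and then: "Apart from this face-to-face meeting there is weekly telephone contact (at a maximum of 15 minutes), initiated by the nurse". The nurse's journal numbers the calls 1 to 8 ("What consecutive number is this telephone contact (1 / 2 / 3 / 4 / 5 / 6 / 7 / 8"). None of its six items concerns adverse events. The only escalation stated there is that suicidal symptoms go to the primary care physician. Usual care has no scheduled nurse contact.

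Both arms share the assessments at 3, 6, 9, 12 and 15 months, including the SCID-I, HRSD-17 and TIC-P (7.1.1, Table 1). On the TIC-P, 7.3 says: "Medical costs that will be assessed include costs related to the intervention, medication use, hospital admissions, and contacts with healthcare professionals". Hospitalisation is one of the SAE criteria in 8.2, which also commits to reporting all SAEs to the ethics committee within 15 days of first knowledge.

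**The concern.** Passive capture depends on how often someone is there to be told. Where one arm talks to a nurse weekly for two months and the other has no scheduled trial contact until month 3, equal true rates can yield unequal records. The text also leaves open whether a practice nurse belongs to the investigator's staff. One reading risks unequal ascertainment, and the other leaves the nurses' information without a path to the record.

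The adverse event record carries most of the safety oversight here. There is no DSMB (8.4), no annual safety report (8.2.2) and no interim analysis (9.6). The duty in 8.1 to act on unforeseen disadvantages and the SAE figures in the annual progress report (11.3) both depend on events reaching the investigator. A hospital admission could sit in the cost data, held by the trial's own researchers, with no one assigned to ask whether it is a reportable SAE.

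**Working it through.** The protocol gives no safety figure to reproduce. The check counts contacts and then illustrates what the imbalance could do.

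**Contacts after randomisation**
- Nurse contacts, intervention arm only (5.1): 1 meeting + 8 calls = 9.
- Shared assessments (7.1.1, Table 1): 5.
- To month 3: 9 + 1 = 10 versus 1. Overall: 9 + 5 = 14 versus 5.

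**Events starting in the call weeks, all five interviews counted.** Assumptions, not document figures: nurses count as staff; true rates are equal; onsets are spread evenly over the eight call weeks, so that k = 1, …, 8 calls remain; each later contact gives an independent chance p of mention.
- Usual care: 1 − (1 − p)^5.
- Intervention: mean over k of 1 − (1 − p)^(k+5).

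| p | Intervention | Usual care | Ratio |
|---|---|---|---|
| 0.2 | 86.4% | 67.2% | 1.28 |
| 0.5 | 99.6% | 96.9% | 1.03 |
| 0.8 | >99.9% | >99.9% | 1.00 |

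For p = 0.2: 0.8^5 = 0.328, so usual care is 0.672. The mean of 0.8^k over k = 1 to 8 is 0.416, so the intervention arm is 1 − 0.328 × 0.416 = 0.864. The ratio is 0.864 / 0.672 = 1.28.

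**Events over the whole follow-up.** A simulation with onsets uniform over 15 months, nurse contacts in weeks 0 to 8 and a chance q of mention at every later contact gave these ratios:

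| q | All events, 15 months | Events in first 2 months | All events, one interview only |
|---|---|---|---|
| 0.1 | 1.10 | 1.48 | 1.40 |
| 0.3 | 1.02 | 1.13 | 1.21 |
| 0.5 | 1.00 | 1.03 | 1.11 |

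The last column lets an event be mentioned at only one interview, the next one, besides any remaining nurse contacts. It represents fading recall.

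**If nurses are not staff.** Scheduled contacts that feed the record are 5 versus 5, and the contact imbalance disappears. Events told to nurses then have no stated route to the record.

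**TIC-P and SAEs, side by side.** Section 7.3 collects admissions as cost data, Table 1 schedules the TIC-P at every assessment without distinction by arm, and 8.2 makes hospitalisation an SAE criterion. No sentence connects them.

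**The case against.** The strongest reply is that the SAEs the protocol expects are not left to chance. Section 8.2 names relapse and the start of other psychopathology. These fall within the SCID-I, held five times in both arms, and 9.2 has recurrence assessed back to the previous assessment. Table 1 also lists somatic illnesses at months 6 and 15 without distinction by arm. This stands, and it confines the ascertainment risk to other events.

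Three stronger readings are tempting, and the protocol does not support them.

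- *Control-arm admissions on the TIC-P are never read as SAEs.* The protocol is silent. Observation by staff could cover an admission seen on a returned questionnaire, since 7.3 has the main researcher and research assistant collect them. Any gap applies to both arms.
- *The comparison of harms is biased by design.* Section 9 plans no between-arm analysis of adverse events, the test in 8.1 is not an arm contrast, and 10.4 rests its low-risk statement on usual care being permitted in both arms. Unequal recording is a risk, and only if nurses count as staff.
- *Equal risks would look like a 1.2- to 3.3-fold excess.* That range comes from stopping at month 3, when usual care has had one contact: 67% versus 20% at p = 0.2 (3.3), 94% versus 50% at 0.5 (1.9), 99% versus 80% at 0.8 (1.2). It drops four later shared interviews and covers only events from about 8 of 65 weeks.

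It can also be said that passive collection is a legitimate choice in a low-risk self-help trial and that log reconciliation belongs in operational documents. That is fair as to detail. But 8.2 itself fixes the collection method, and a better one is available at interviews already planned.

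**Conclusion.** The point holds in limited form. Section 8.2 fixes passive collection alongside 14 versus 5 scheduled contacts and does not say whether nurses are staff. If they are, events other than those the SCID assesses are at risk of being recorded more often in the intervention arm, mainly in the first three months. If they are not, the gap is a missing route for what nurses hear.

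For events starting in the call weeks, the ratio is about 1.3 at a 0.2 chance of mention per contact and about 1.0 at 0.5 or more. Over 15 months the simulation gives 1.00 to 1.10, or 1.11 to 1.40 if only the next interview counts. All of these rest on equal true rates and an assumed chance of mention that the protocol cannot supply.

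The missing review of TIC-P admissions is a separate gap. It affects both arms alike and concerns completeness of SAE reporting, not balance between arms.

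**What to change.** Amend 8.2 as follows.

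1. Ask both arms the same standard question on adverse events and the SAE criteria at each existing 3, 6, 9, 12 and 15 month interview. This gives 5 common ascertainment points per arm.
2. Base any by-arm safety summary on those answers.
3. List events known only from nurse contacts separately. This requires 8.2 to say how nurses pass such events to the trial.
4. When a TIC-P is received, check every reported hospital admission, in both arms, against the SAE log.

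The cost is about a minute per interview, more minor events on record and one routine data query. No additional visit is needed.

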### 8.2.1. Suspected unexpected serious adverse reactions (SUSAR)

*N/A*

### 8.2.2. Annual safety report

*N/A*

## 8.3 Follow-up of adverse events

All adverse events will be followed until they have abated, or until a stable situation has been reached. Depending on the event, follow up may require additional tests or medical procedures as indicated, and/or referral to the PCP or a medical specialist.

## Data Safety Monitoring Board (DSMB)

N/A

# *9.* STATISTICAL ANALYSES

## 9.1 Descriptive statistics

Standard descriptive methods (e.g., frequencies and percentages or mean ± SD) will be used to summarize the demographic and clinical features of the controls and the patients who received the intervention.

All calculated *P* values are 2 sided; statistical significance will be set at *P* <.05.

**9.3 Economic evaluation**

For the valuation of health care utilization standard prices published in the Dutch costing guidelines will be used49. Medication use will be valued using prices of the Royal Dutch Society for Pharmacy. Unit prices of the different intervention elements will be calculated using a bottom-up approach. Costs for personnel, patient materials, rental of practice spaces and other expenses will be included in these calculations. Costs and effects are not discounted.

Missing cost and effect data will be imputed using multiple imputation according to the MICE algorithm developed by van Buuren50. Costs typically have a highly skewed distribution. Policy makers want to have information on the difference in mean total costs between the two treatment groups to be able to estimate the total health care budget needed for a specific condition. 51 Therefore, bias-corrected and accelerated bootstrapping with 5000 replications will be used to calculate 95% confidence intervals around the mean difference in total costs between the treatment groups.

The economic evaluation will be conducted from a societal perspective, both as a cost-effectiveness analysis (CEA, with depression-free person years as the clinical end term) and as a cost-utility analysis (CUA, with incremental costs per quality adjusted life years (QALY) gained) as the clinical end-term. Bootstrapping will be used to estimate the uncertainty surrounding the ICERs which will be graphically presented on cost-effectiveness planes. Cost-effectiveness acceptability curves and net monetary benefits will also be calculated. Cost-effectiveness acceptability curves show the probability that collaborative care is cost-effective in comparison with usual care for a range of different ceiling ratios thereby showing decision uncertainty.52

These analyses help to answer the question whether the intervention offers good value for money.

**9.4 Analysis of secondary clinical outcomes**

Moderator analyses will be conducted for some demographic variables. Subgroups that show particularly good response to the intervention will be identified by regressing HRDS depression severity on the interaction term of treatment and clinical characteristics of the patients as measured at baseline. Examples of other characteristics are number of previous depressive episodes, treatment preference, age of onset of first depression, self-efficacy in preventing depression, pain and fatigue, social economic status other demographic characteristics like gender, marital and occupational status and age.

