**Secondary Objective(s):**

To study whether nurse-led self-help for patients with recurrent MDD versus usual care alone:

A) reduces health care utilisation

B) is effective in reducing co-morbid distress, anxiety and somatisation

C) is satisfying according to patients

D) is (cost)-effective in certain subgroups of patients, particularly related to (i.e. modified by):

- the number of previous episodes

- type of treatment for the last recurrence (AD, psychological intervention, nothing etc).

- the severity of residual depressive symptoms in the remitted phase

- age of onset of the first depressive episode,

- social economic status (education)

- self-efficacy for managing depression

- symptoms of pain and/or fatigue

- long duration of individual episodes

- socio-demographic factors such as age and gender

- pattern use of antidepressants

The secondary objectives lead to the hypotheses below about effect modification.

*RE: Reduction in health care utilisation*

The substantial economic burden of depression is partly due to an increased health care utilisation. Evidence shows that health care costs of depressed patients are higher compared with matched controls even after adjusting for co-morbidity30. This is not only true for mental but also for general medical care utilization. Therefore, it is hypothesized that by preventing recurrences through this intervention, health care utilisation and related costs in these patients will also be reduced.

*RE: B (cost-) effective in reducing co-morbid levels of psychopathology*

Psychiatric comorbidity in depression is associated with greater symptom severity, severer functional impairments and a more chronic course of the disease. Comorbid psychopathology in depressed patients is common and often involves anxiety and somatisation.

Anxiety consists of irrational and diffuse fears and avoidance behaviour. Somatisation consists of a range of psychosomatic symptoms like headache, muscle pains, cardiovascular and gastrointestinal symptoms31. It is hypothesized that with the reduction of (risk for) recurrences, the co-morbid level of anxiety and/or somatisation will also decrease.

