Besides fatigue, also the prognosis of depression and comorbid pain is poor compared with the prognosis for individuals with depression without pain 35. Pain with comorbid depression appears to be additive in terms of an increased number of medical visits and higher health care costs. In this study, both fatigue and pain are assessed to evaluate their possible relation with the overall outcome in terms of cumulative incidence of depression and total healthcare costs.

Both number of previous episodes and type of previous care are used for stratification allowing us to study these factors as potential effect modifiers.

An earlier first onset of depression (i.e. at a younger age) is associated with a poorer prognosis regarding the course of the depression (more recurrences, chronicity). One suggestion therefore is that early onset disorders typify a subset of patients with a distinct etiological profile in which genetic vulnerability and early developmental aspects play a larger role36. A large, recent Dutch study (NESDA) already confirmed that early onset disorders – apart from severity and duration – seem to result in poorer prognosis37.

The higher prevalence of depression in the lower socioeconomic strata (SES) suggests that there is a negative association between depression and socioeconomic status. The process linking SES and depression might be based on 2 personal resources: income and education. Higher-SES individuals are better endowed with such resources, leading to better health outcomes. A better health outcome (fewer recurrences) due to a higher level of education might be explained by higher levels of the patients’ self-efficacy for self-management of depression in these patients. Self-efficacy refers to the perceived ability to produce a desired action and captures both self-esteem (evaluation of own worth) and self-mastery (evaluation of self-command. Above average levels of self-efficacy is protective in the onset of depressive disorders38.

The hypotheses in this trial are that SES (in terms of attained education level) and depression are negatively correlated and that higher SES, via self-efficacy, is positively associated with better treatment response.

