**9.5 Analyses of secondary economic outcomes**

Analogous to the moderator analyses for clinical end-terms, an incremental net benefit regression (INBR) analysis will be conducted to addresses the research question in what groups the intervention is likely to be particularly cost-effective. The same set of predictor variables (see above) will also be used in these INBR analyses.

The Incremental Net Benefit will be calculated as Eλ –C. The first term is the number of units of effectiveness gained multiplied by an unknown quantity (λ) what one is willing to pay (WTP) for a unit of effectiveness gained. Because λ is unknown, we will use a likely WTP-range. The product term is subtracted by the costs yielding the net benefit expressed in monetary terms. Incremental net-benefits will be obtained using a regression analysis approach and these help to identify moderators (sub-groups) for which the intervention is particularly cost-effective53.

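### Section 9.4 names responder subgroups from 11 to 15 interaction tests with a blanket P<.05 as the only significance rule: about a 43–54% chance of at least one false subgroup on HRSD if the tests are independent

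*Protocol*

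**What the plan says.** Secondary objective D in section 2 asks whether the intervention "is (cost)-effective in certain subgroups of patients, particularly related to (i.e. modified by" ten listed items. Further on, section 2 singles out two of them: "Both number of previous episodes and type of previous care are used for stratification allowing us to study these factors as potential effect modifiers".

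Section 9.4 gives the clinical analysis: "Subgroups that show particularly good response to the intervention will be identified by regressing HRDS depression severity on the interaction term" of treatment and baseline clinical characteristics (HRDS there is the HRSD of the other sections). The list is open: "Examples of other characteristics are number of previous depressive episodes, treatment preference, age of onset of first depression", followed by self-efficacy, pain, fatigue, socio-economic status, gender, marital status, occupational status and age.

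Section 9.5 carries this over to the incremental net benefit regression (INBR): "The same set of predictor variables (see above) will also be used in these INBR analyses". That analysis runs over a range of willingness-to-pay (WTP) values whose number is not stated.

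Section 9.1 holds the only significance rule in the protocol. All calculated P "values are 2 sided; statistical significance will be set at" P<.05. No section calls the moderator analyses exploratory or says how a significant interaction among many is to be read.

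**The concern.** Section 9.4 does more than describe interactions. It says that subgroups will be identified from them. Read with section 9.1, the natural working rule is that a subgroup is named when its interaction has P<.05. Applied to a long, open list, that rule will often name a subgroup by chance.

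Objective D bears on who should be offered nurse-led self-help. A chance finding reported as a subgroup with particularly good response could steer that choice, and the plan as written gives the reader no means of discounting it.

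**Working it through.** The protocol states no familywise error rate, so there is no figure of its own to reproduce.

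**Inputs from the protocol**
- Level: two-sided .05 for every calculated P value (section 9.1).
- Named in section 9.4: previous episodes, treatment preference, age of onset, self-efficacy, pain, fatigue, socio-economic status, gender, marital status, occupational status and age. That is k = 11.
- Added by objective D: type of treatment for the last recurrence, residual symptoms, episode duration and pattern of antidepressant use. That is 11 + 4 = 15.
- The Summary also lists satisfaction with PCT. It is measured after baseline and only in intervention patients, so it cannot be a baseline interaction term and is left out.

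**Assumptions not in the protocol:** one test per moderator in its own model, one HRSD time point, no true effect modification, and the correlations shown below.

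**HRSD alone, independent tests:** P(at least one false subgroup) = 1 − 0.95^k.
- k = 11: 1 − 0.95^11 = 1 − 0.569 = 43%. Expected false positives: 11 × 0.05 = 0.55.
- k = 15: 1 − 0.95^15 = 1 − 0.463 = 54%. Expected false positives: 15 × 0.05 = 0.75.

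A significant interaction in either direction leaves one end of the moderator responding better, so the full two-sided 5% per test counts.

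**HRSD alone, correlated moderators.** Drawing equally correlated normal test statistics (200,000 draws) gives 37% (k = 11) and 46% (k = 15) at correlation 0.3, and about 30% and 36% at correlation 0.5. A patient-level simulation used N = 238 and 268, one third of the moderators binary, a constant treatment effect and 2,000 runs. It gave 44% (k = 11) and 52–54% (k = 15) at correlation 0, and 38–39% and 48% at correlation 0.3.

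**HRSD plus net benefit.** This applies only if the section 9.5 interactions are also tested at .05, at one WTP value. With every test independent, the result is 1 − 0.95^22 = 68% and 1 − 0.95^30 = 79%. With correlation:

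| Correlation among moderators | Correlation HRSD/net benefit | 11 moderators | 15 moderators |
|---|---|---|---|
| 0 | 0 | 68% | 79% |
| 0 | 0.7 | 62% | 73% |
| 0.3 | 0.3 | 60% | 70% |
| 0.5 | 0.5 | 49% | 57% |
| 0.5 | 0.7 | 46% | 53% |

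Over moderator correlations of 0 to 0.5 and outcome correlations of 0 to 0.7, the pooled chance runs from about 46% to 79%. More WTP values or follow-up times would raise it.

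**With a correction.** Bonferroni within the HRSD set tests at 0.05/11 = 0.0045 or 0.05/15 = 0.0033. Under independence with 11 tests the familywise rate is 1 − (1 − 0.0045)^11 = 4.9%. The patient-level simulation gave 4–6%.

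**The case against.** The strongest reply is that multiplicity handling and exploratory labels for secondary analyses usually belong in the SAP, which is not at hand. Their mere absence from the protocol is indeed no finding. But this protocol sets a level for every P value and says that subgroups will be identified. An SAP that labelled or corrected these tests would have to depart from sections 9.1 and 9.4.

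Second, no sentence says that a subgroup is named when P<.05. The rule comes from joining sections 9.4 and 9.1, and 9.1 is headed as descriptive statistics. That is fair: for HRSD the rule is an inference, though no other criterion is on offer. For net benefit the inference is weaker. Section 9.5 has no test criterion and says only that the regression helps to identify moderators. Its reference to the predictors above also points most naturally to the 11 in section 9.4.

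Third, a reader might infer that the plan names a false subgroup more often than not, or in some 60–77% of trials. The documents do not support that. Figures of that size pool the clinical and economic analyses under chosen correlations. On HRSD alone the chance passes one half only from 14 independent tests (1 − 0.95^13 = 49%, 1 − 0.95^14 = 51%), so not for the 11 named in section 9.4.

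Fourth, a reader might infer that all moderators are treated alike. Section 2 says otherwise. It singles out the two stratification factors and gives reasons for others, such as residual symptoms. Those reasons do not lower the error rate of an uncorrected set, and section 9.4 does not carry the priority through. It lists previous episodes as one example among many and leaves out type of last treatment.

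Finally, section 4.4 powers the trial for the overall recurrence difference only. Promoting a few interactions to confirmatory tests would therefore be hard to defend. This stands, and it shapes the fix.

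**Conclusion.** The concern holds for the HRSD moderator analysis. Following sections 9.1 and 9.4 as written carries a 43–54% chance of at least one false subgroup if the tests are independent, and about 37–48% at a moderator correlation of 0.3, against a nominal 5% per test. This assumes one .05 test per moderator and no true modification.

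The pooled 46–79% is conditional. It needs the net-benefit interactions to be tested at .05 too, and it rests on assumed correlations. It should be quoted only with those conditions.

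The primary analysis is unaffected. Nor does the point show that objective D is unanswerable. It shows that a single P<.05 from this list is weak evidence for a subgroup, and that the plan should say so. It is a point that should be corrected, at low cost.

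**What to change.** - **Sections 9.4 and 9.5:** label the moderator analyses exploratory. Replace the open examples with one list that agrees with objective D. Report every listed interaction as an estimate with a 95% CI, and state that no subgroup is declared identified on an uncorrected P<.05.
- **Section 9.1:** state that the .05 rule does not apply test by test to the moderator analyses.
- **Priority:** give the two stratification factors, number of previous episodes and type of treatment for the last episode, first place in interpretation, in line with section 2, and name the second of them in section 9.4.
- **Optional:** if the sponsor wants a firm subgroup claim, apply Holm over the prespecified set for that outcome.

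This is a wording change with no extra data or patients. The cost is fewer firm subgroup claims and, if Holm is used, lower power for any single moderator.
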